### Study procedures, randomization, and follow-up

The study protocol has been approved by the medical ethics committee of the TweeSteden Hospital as well as by the local regulatory authority of the TweeSteden Hospital. The trial conforms to the principles most recently outlined in the Declaration of Helsinki (2008). All patients will be informed orally and in writing about the purpose, rights, and possible benefits/risks of the study prior to participation. We have guaranteed full participation of the HF outpatient clinic of the TweeSteden hospital. Eligible patients will be invited to participate in the study during a regular visit to the HF nurse or cardiologist at the HF outpatient clinic. After 4 to 7 days patients will be contacted by telephone and asked for participation. Positively responding patients will then sign the informed consent forms and receive an appointment at the HF outpatient clinic within two weeks for their baseline visit (T0).

Patients will be randomly assigned following a blocked randomization procedure (computerized random numbers) to either the intervention arm or to usual care (1:1). Due to the restriction of a limited number of MASS devices at our disposal, the randomization procedure will be performed per week so that each week a maximum of 6 patients is assigned to either condition arms. In order to prevent selection bias, the allocation sequence will be concealed from the researcher and the HF nurse enrolling and assessing patients in sequentially numbered, opaque, and sealed envelopes. A second researcher working outside the hospital will develop and monitor the concealment system.

All patients will visit their HF nurse for their first usual care visit (T0). Corresponding envelopes based on the order of inclusion sequence will be opened only after completion of all baseline assessments during this visit to allocate the intervention. If the patient has been randomized to the intervention group, he/she will receive the MASS device and instructions, and will be fully explained how to use it. The intervention period starts within two weeks after this visit, for a period of 6 months (see below for specific details on intervention).

All patients will return to the HF outpatient clinic with a three-monthly frequency, meaning that in total three usual care visits are included in the intervention period. After the intervention period, all patients will continue to receive usual care, and will participate in four follow-up occasions at 9 (T2), 12 (T3), 15 (T4), and 18 months (T5) post-baseline that coincide with the regular three-monthly clinic appointments.

Every six months (i.e. at baseline (T0), at the end of the intervention (T1), and at 6 (T3) and 12 (T5) months thereafter), the following activities will take place in both study conditions: (i) a blood draw assessment of biochemical variables; (ii) a six-minute walk test; (iii) a NYHA functional class determination following standardized protocol; and (iv) an echocardiography to determine LVEF (%). The follow-up at 3 and 9 months will consist of a telephone call, only requesting information on healthcare consumption and adherence. The timeline of the study design is demonstrated in Figure 1.

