## Study design

The TELEMED-HF study is a Dutch, open, prospective, randomized, controlled clinical intervention trial (RCT) designed to improve medication adherence using a telemonitoring solution in a large group of HF patients. Primary and secondary outcomes will be evaluated pre- and post-intervention with a follow-up of 12 months. The trial has been registered at http://www.ClinicalTrials.gov (NCT01347528). TELEMED-HF is expected to report its first results in autumn 2013.

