### Event adjudication

An independent, blinded, clinical endpoint committee will classify the number of all-cause and cardiac-related deaths.

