### Intervention

Patients in the intervention group will be instructed to use an electronic medication adherence monitor, the MASS device, for a 6-month period and to visit the HF outpatient clinic of the TweeSteden hospital 3 times (usual care). MASS (a) dispenses all prescribed medication in the right dosage at the specified time, (b) reminds patients to take their medications through an alarm, sms or voicemail service and records adherence, and (c) sends critical data about non-adherence to the HF nurse, via a web application (CarebyWeb). The MASS device will be provided to the patient during the baseline visit, including an instruction how to use it and a manual for technical support. The patients in the intervention group will then take the monitor home and will collect a medication roll from their own pharmacy within one week. In a weekly notebook, patients will report on their perceived adherence, answer some dedicated questions on medication side-effects, satisfaction with MASS, and disease-specific and generic perceived health. After 6 months, patients will return their monitor to the researcher during their usual care visit (T1).

Recordings from the MASS device to CarebyWeb will be used as follows: (1) > 3 alerts will result into contact by the HF nurse with the patient outside regular appointments to identify reasons for not taking the medication as prescribed; and (2) if any inconsistency in medication taking behavior is being observed, the HF-nurse will use this information at the patient's next regular visit at the HF outpatient clinic to discuss reasons for non-adherence and ways to address them.

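### After T0 the staff described as assessing patients know the arm, and the article states no masked assessment of follow-up NYHA class, 6-minute walk or LVEF

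*Protocol article*

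**What the plan says.** All places are in the protocol article.

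- **Study design** calls the study a "Dutch, open, prospective, randomized, controlled clinical intervention trial".
- **Study procedures, randomization, and follow-up** keeps the allocation sequence "concealed from the researcher and the HF nurse enrolling and assessing patients". Envelopes are "opened only after completion of all baseline assessments during this visit to allocate the intervention".
- **Intervention** says that the device "sends critical data about non-adherence to the HF nurse" through CarebyWeb. More than three alerts lead the nurse to contact the patient, and recorded irregularities are taken up at the next regular visit. On the device itself: "After 6 months, patients will return their monitor to the researcher during their usual care visit (T1".
- **Study procedures, randomization, and follow-up** schedules a walk test, an NYHA determination by a standardized protocol and "an echocardiography to determine LVEF" at T0, T1, T3 and T5 in both arms. Table 1 lists these as secondary outcomes. NYHA and LVEF are coded as routine-care measures and the walk test as an additional assessment.
- **Event adjudication** contains the only masked step in the article: "An independent, blinded, clinical endpoint committee will classify the number of all-cause and cardiac-related deaths".

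**The concern.** Concealment and masking do different jobs. Sealed envelopes stop staff from choosing who enters which arm. They do nothing for measurements made after the envelope is opened. Here the role that assesses patients is also the role that monitors the device, and device monitoring exists in one arm only.

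NYHA class is a judgement. Walk distance depends on effort and on encouragement. LVEF depends on how a reader measures the images. An observer who knows the arm can shift any of the three, in either direction.

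Walk test, NYHA and LVEF are also the only secondary outcomes in Table 1 that are not questionnaires. The remaining one, the KCCQ, is completed by patients who know their arm. So no secondary outcome has a stated masked assessment.

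The first secondary objective adds a second route. It relates adherence to disease severity and physical functioning. In the MASS arm the nurse knows each patient's recorded non-adherence as well as the arm, and that knowledge could colour the measurements to which adherence is then related.

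**Working it through.** The article gives no figure on this point, so there is nothing of the plan's own to reproduce. The check is to follow who knows the arm, and when.

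| Occasion | Does the HF nurse know the arm? | Does the researcher know the arm? | Masked measurement stated? |
|---|---|---|---|
| T0 measurements | No, envelope still sealed | No | Not needed |
| After T0 | Yes, receives and acts on CarebyWeb data | Not stated before T1 | – |
| T1 measurements | Yes | Yes once the monitor is handed in; order relative to the measurements not stated | No |
| T3 and T5 measurements | Yes, nothing re-masks | Yes, nothing re-masks | No |
| Deaths | – | – | Yes, blinded committee |

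The remaining link is who makes each measurement. The randomization paragraph describes these staff as assessing patients. No section assigns the walk test, the NYHA grading or the echocardiogram reading to a named role. NYHA comes from routine visits, which are consultations with the HF nurse, so exposure is most plausible there. The walk test is a study-specific addition, probably run by the same small team. For the echocardiogram there is no indication either way.

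**Illustration of size, under assumptions.** Inputs: 200 per arm (Abstract); SDs of 100 m for the walk and 8 points for LVEF (assumed); no true effect; a fixed observer shift in one arm (assumed); an unadjusted two-sided 5% test of means.

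- SE = SD × √(2/200) = 0.1 × SD, so 10 m and 0.8 points.
- False-positive rate = P(|Z + shift/SE| > 1.96).
- Walk, 10 m: shift/SE = 1, rate = P(Z > 0.96) + P(Z < −2.96) = 0.169 + 0.002 = 17%.
- Walk, 20 m: shift/SE = 2, rate = 52%.
- LVEF, 1 point: shift/SE = 1.25, rate = 24%.
- LVEF, 2 points: shift/SE = 2.5, rate = 71%.

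Only the ratio of shift to SD matters. If the walk shift were 5 m, or the SD twice as large with a 10 m shift, then shift/SE = 0.5 and the rate is P(Z > 1.46) + P(Z < −2.46) = 0.072 + 0.007 = 8%. The result therefore runs from near nominal to very large over ratios that the documents cannot narrow.

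**The case against.** The strongest reply is that much of this rests on what a condensed article leaves out. The trial is openly declared open, the full protocol is not shown, and the echo reader's identity is the kind of detail an article omits. Several parts of that reply stand:

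- **LVEF.** A reader might infer that LVEF is measured with allocation known. The article does not say so. An echo reader outside the nurse and researcher team is not excluded.
- **Baseline.** A reader might take the problem to cover all measurements. It does not, because T0 assessments are completed before the envelope is opened.
- **The concealment sentence.** It is sound for its stated purpose, preventing selection bias. It is cited here only because it says who assesses. Grammatically, the assessing could belong to the nurse alone. The exposure through CarebyWeb is the nurse's in any case.
- **Device instruction.** That the nurse instructs MASS users might be inferred, but no section names the instructor. The argument does not need it.
- **Device return.** The monitor is returned at the T1 usual care visit. The Usual care section describes a half-hour consultation and mentions neither echocardiography nor a walk test. The documents do not show that the hand-over comes before the tests.
- **NYHA.** A standardized protocol already exists. It limits variability but does not mask the grader.
- **The percentages.** The Statistical analysis section specifies no between-arm test for LVEF, NYHA class or walk distance, so they are not error rates of a planned test.

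The reply does not remove the core. The article does treat the subject: it describes concealment in detail and gives deaths a blinded committee. It also places assessing and device monitoring in one role and sets the device return at T1. These are stated choices that work against masking, and who assesses outcomes is a matter of trial conduct, not of the analysis plan.

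**Conclusion.** The point holds for the T1, T3 and T5 measurements. After T0 the HF nurse knows the arm by design, the researcher knows it at the latest when the monitor comes back, and the only masked step stated is the classification of deaths. The exposure is clearest for NYHA class and the walk test. For LVEF the defensible statement is that no masked reading is described.

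The consequence is confined to secondary endpoints, and to the secondary objective that relates adherence to them. The size of any bias cannot be derived from the documents. The figures of 8% to 71% show how sensitive a simple comparison of 200 per arm would be under assumed SDs and shifts, and nothing more. The point does not imply that LVEF should be promoted to lead measure of disease severity.

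**What to change.** With existing staff, add the following to the study procedures:

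1. Name the role that makes each T1, T3 and T5 measurement and say whether it is masked.
2. Have the T1, T3 and T5 echocardiograms measured from recordings or requests that do not show the arm, by a reader without CarebyWeb access. If this is already the practice, one sentence settles it.
3. Use one fixed script for the walk test in both arms, and apply the existing standardized NYHA protocol before any MASS data are discussed at that visit.
4. Take the monitor back only after the T1 measurements, and not through the person making them.
5. Where masking is not possible, report NYHA and walk-test results as assessed with the arm known.

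The handling of alerts during the intervention stays as it is. The cost is procedure wording, a change of order at T1 and minor scheduling effort, with no added visits or tests. Masking of NYHA and the walk test will remain partial, since patients can reveal their arm and the nurse may already have contacted them about alerts.

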**Figure 1 F1:**
[figure not shown]
**Timeline study procedure**. The figure shows a timeline of the study procedure.

Over the 18-month study period as well as the year before inclusion, retrospective refill rates will be requested from the patients' pharmacies. The general practitioner of the patients will be informed of the patients' participation in the study and will be asked to report the total number of patient visits to their clinic by filling out a patient contact form sent by us every 6 months.

### Study endpoints

The main study parameters include objective and subjective medication adherence, number of hospitalizations, healthcare consumption and costs (see Table 1). Objective medication adherence will be assessed using the monitor output collected in a web-based application (CarebyWeb), and the prescription refill records provided by the patients' pharmacies. A cost-benefit analysis will be assessed by means of the TiC-P questionnaire[20] and event rate (and related DBC (diagnosis treatment combination, the Dutch system to allocate costs to treatments of specific patient groups)). The TiC-P questionnaire will enable us to compare healthcare consumption in the intervention and control group.

**Table 1 T1:** Measures & design

Construct/Measure	Methods of assessment	T0 Pre	T1 Post	T2	T3	T4	T5
*Primary outcomes*							
Adherence	Objective: Monitor output	X	X				
	Refill rate pharmacy	MR	MR		MR		MR
	Subjective: MAS, MOS-adhere	Q	Q	T	Q	T	Q
Healthcare Consumption	Number of rehospitalisations, time to first HF-related hospitalization, visits to the GP and ER due to cardiac causes, DBC codes	MR	MR	MR	MR	MR	MR
	TiC-P,	Q	Q	T	Q	T	Q
*Secondary outcomes*							
Physical function,	6-minute walk test	A	A		A		A
disease progression	NYHA, LVEF	S	S		S		S
Quality of life	KCCQ	Q	Q		Q		Q
*Predictors*							
Sociodemographic	Self-report, postal code area	Q					
Self-care behavior	EHFScBS-9	Q	Q		Q		Q
Cognitive function	MMSE	A	A		A		A
Depression	PHQ9, BDI10	Q	Q		Q		Q
Anxiety	GAD7, SAD4	Q	Q		Q		Q
Type D personality	DS14	Q	Q				

NB. Multiple instruments are used to assess anxiety and depression since there is no gold standard or consensus which instruments to use in patients with somatic disease. All psychological questionnaires are standardized and validated. Variables obtained from: S = standard measures in routine clinical care visits, A = additional assessment physical/cognitive functioning, MR = medical records, Q = questionnaire, X = intervention, T = telephone call.

The main secondary study parameters include QoL, disease severity (NYHA functional class determination following standardized protocol; LVEF using echocardiography), and exercise capacity (six-minute walk test; see also Table 1). Other secondary variables are designed to determine whether randomization was successful, to assess their potentially moderating influence on adherence, and to generate risk profiles of patients who may or may not benefit from the intervention (see Table 1). These include: (1) psychological and sociodemographic variables; i.e. Type D personality, depression, anxiety, socio-economic status, age, gender, beliefs in medication, self-care behavior, and cognitive function; and (2) clinical variables; i.e., self-reported medication side effects; time since HF diagnosis; HF etiology; previous cardiac events (MI), previous cardiac procedures (PCI, CABG), previous cardiac devices (ICD, pacemaker), number of hospitalizations for HF; blood pressure; cholesterol; triglycerides; diabetes; atrial fibrillation; comorbidities; cardiac medication, other medication (including psychotropic medication); C-reactive protein; NT-pro-BNP; parameters measured in standard clinical practice (including liver function (ACAT, ALAT, Gamma GT), hemoglobin, hematocrit, leukocytes, and kidney function (urea and creatinine).

All endpoints will be assessed with standardized and validated measures shown to have good psychometric properties, usual care laboratory tests, physical examinations, and pharmacy refill records (Table 1).

### Event adjudication

An independent, blinded, clinical endpoint committee will classify the number of all-cause and cardiac-related deaths.

### Intervention

Patients in the intervention group will be instructed to use an electronic medication adherence monitor, the MASS device, for a 6-month period and to visit the HF outpatient clinic of the TweeSteden hospital 3 times (usual care). MASS (a) dispenses all prescribed medication in the right dosage at the specified time, (b) reminds patients to take their medications through an alarm, sms or voicemail service and records adherence, and (c) sends critical data about non-adherence to the HF nurse, via a web application (CarebyWeb). The MASS device will be provided to the patient during the baseline visit, including an instruction how to use it and a manual for technical support. The patients in the intervention group will then take the monitor home and will collect a medication roll from their own pharmacy within one week. In a weekly notebook, patients will report on their perceived adherence, answer some dedicated questions on medication side-effects, satisfaction with MASS, and disease-specific and generic perceived health. After 6 months, patients will return their monitor to the researcher during their usual care visit (T1).

Recordings from the MASS device to CarebyWeb will be used as follows: (1) > 3 alerts will result into contact by the HF nurse with the patient outside regular appointments to identify reasons for not taking the medication as prescribed; and (2) if any inconsistency in medication taking behavior is being observed, the HF-nurse will use this information at the patient's next regular visit at the HF outpatient clinic to discuss reasons for non-adherence and ways to address them.

### Usual care

Patients randomized to the usual care arm will receive the care as it is normally offered consisting of three visits (0, 3, and 6 months after inclusion) to the HF outpatient clinic of the TweeSteden hospital for a consultation with the HF nurse. During this half hour visit, anamnesis will be taken, a physical examination will take place, and topics like medication adherence, and anything the patient additionally wants to discuss will be addressed. Patients will be treated for their HF in accordance with the current Dutch guideline for treatment of patients with chronic HF [4].

### Statistical analysis

This trial is designed to show whether the MASS device is effective in improving medication adherence in a chronic HF population compared to usual care only. Descriptive statistics (frequencies, means (±SD) will be calculated stratified by experimental group (intervention vs. usual care). T-tests for continuous variables and Chi-square tests for categorical variables will enable us to compare baseline values for both groups to formally test the successfulness of the randomization procedure. We will examine the effectiveness of the intervention by using the intention-to-treat principle, with the inclusion of all randomized participants in the statistical analyses regardless of whether they completed the intervention or the follow-up measurements. Missing data will be imputed using regression imputation techniques. The equality of subjective and objective adherence will be assessed by means of Intraclass correlation and Cohen's measure for agreement, the Kappa statistic, depending on the measure of adherence. Repeated measures analysis of covariance will be used to assess differences between the intervention and control group with respect to changes in adherence over the six-month intervention period, and to assess long-term effects (up to one year post-intervention) of the intervention on medication adherence, while taking potential confounders into account. To determine whether the time to hospitalization is longer for patients using the MASS device compared with patients in the control group, the log-rank test for comparison of Kaplan-Meier curves will be used. In addition, Cox proportional hazards regression modeling will be used to determine whether the usage of the MASS device predicts time to the first event (i.e. hospitalization due to HF or cardiac-related death). Multivariate regression analyses will be used to assess which psychological, clinical, demographic, and/or medication-related determinants predict adherence (with the percentage of adherence as dependent variable) in chronic HF patients and moderate the effects of the MASS device on patient adherence. The influence of potential effect modifiers will be examined by means of interaction terms.

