### Statistical power analysis

The most demanding analysis in this trial with regard to statistical power and sample size is the survival analysis in which adherence is a predictor of the number of HF-related hospitalizations. A power analysis in PASS for a Cox proportional hazard regression model [21] was performed, using information from the TweeSteden hospital and previous studies. Assuming an event rate of 29% (data 2008 and 2009, TweeSteden hospital), an estimated hazard ratio of between .70 and .80 [6], taking into account an SD of 1 for our main predictor adherence, and a correlation with covariating factors of on average .30, a two-sided type I error of .05, and a minimal power of 80% to detect a HR of .70, the sample size needed for this study to be sufficiently powered is 400. In an earlier study conducted at the same outpatient clinic and within the same patient population, a response rate of 78.3% was shown with a 19.9% attrition rate [22]. Thus, in order to achieve the calculated sample size of 400 patients, we intend to include 480 patients at baseline (1:1). Based on a more conservative response rate of 70%, 685 patients need to be approached. With 400 patients visiting the outpatient clinic each year (approximately 3-5 new patients/week) inclusion of such a number within two years is feasible. This sample size is also sufficient to test the other, less power demanding, research questions.

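### If regression imputation is done as single imputation, the adherence ANCOVA either rejects too often (up to about 10-12% at a nominal 5%) or understates the effect by about a fifth

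*Protocol article*

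**What the plan says.** All of this is in the protocol article. Under Statistical analysis, the intention-to-treat rule is given as "with the inclusion of all randomized participants in the statistical analyses regardless of whether they completed the intervention or the follow-up measurements". The next sentence is the whole missing-data plan: "Missing data will be imputed using regression imputation techniques". The test it feeds follows shortly after: "Repeated measures analysis of covariance will be used to assess differences between the intervention and control group with respect to changes in adherence". It is applied both to the first six months, while the device is in use, and to the year after that.

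Nothing there says whether imputation is single or multiple, whether a random residual is added, which predictors enter the imputation model, whether arm is one of them, or how imputation uncertainty reaches the standard error.

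Under Statistical power analysis, an earlier study at the same clinic is cited: "a response rate of 78.3% was shown with a 19.9% attrition rate". Enrolment is raised from 400 to 480 on that account. Table 1 lists adherence as a primary outcome, measured by monitor output, pharmacy refill rate (from records) and two self-report scales (by questionnaire or telephone).

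**The concern.** In ordinary usage, regression imputation replaces each missing value by a prediction from a fitted model. If this is done once and the completed data are passed to a standard ANCOVA, the analysis treats the predictions as measurements. The sample size is overstated. If no random residual is added, the residual variance is understated as well.

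The consequence depends on a choice that the plan leaves open. If arm is in the imputation model, the arm difference is carried into the imputed values and the standard error is too small, so p-values and intervals are too favourable. If arm is left out, the imputed values carry no arm difference and the estimate is pulled towards zero.

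Adherence is the outcome that the trial is designed to improve, so either fault reaches the central comparison. This is a stated method with a known defect, not just a detail left for later.

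**Working it through.** **Inputs from the article.** Missing share m = 0.199, taken from "a response rate of 78.3% was shown with a 19.9% attrition rate"; r = 1 − m = 0.801. N = 400 or 480. Two-sided level .05. The article states that level only for the Cox calculation ("a two-sided type I error of .05, and a minimal power of 80% to detect a HR of .70"), and I assume it for the adherence test too. The article gives no rejection rate under imputation, so the nominal 5% is the only benchmark.

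**Assumptions.** Normal outcome, values missing completely at random and equally in both arms, baseline-outcome correlation 0.5 unless stated, ANCOVA on baseline and arm.

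**Formulas.** Let σ² be the residual variance given baseline. With 1:1 allocation, the arm effect from N complete patients has variance 4σ²/N. Let V be the true variance divided by the reported variance. The actual rejection rate under no effect is 2[1 − Φ(1.96/√V)].

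- *Deterministic, arm in the model.* Imputed points lie on the fitted line, so the estimate equals the observed-data estimate, with true variance 4σ²/(rN). The residual sum of squares does not grow but is divided by about N instead of rN, so the reported variance is 4rσ²/N. Hence V = 1/r².
- *Random residual added once, arm in the model.* True variance is (4σ²/N)(1/r + m) and reported variance is 4σ²/N. Hence V = 1/r + m.
- *Deterministic, arm omitted.* The estimate is r times the observed-data estimate. True and reported variance are both 4rσ²/N, so V = 1, but the effect is multiplied by r.

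**Results at m = 0.199.**

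- Deterministic, arm in: 1.96 × 0.801 = 1.570, giving 11.6%. Simulated: 11.47% (N = 480) and 11.55% (N = 400).
- Random residual, arm in: V = 1.248 + 0.199 = 1.447, √V = 1.203, 1.96/1.203 = 1.629, giving 10.3%. Simulated: 10.29% and 10.12%.
- Deterministic, arm in, testing the change from baseline: 9.0%, 9.7% and 10.5% at baseline correlation 0.3, 0.5 and 0.7.
- Arm omitted: 5.0% by formula; simulated 5.05% and 4.77% (deterministic), 4.62% and 4.98% (random residual). A true difference of 0.25 SD becomes 0.801 × 0.25 = 0.200 SD; simulated 0.200. Power for that difference at N = 480 is 80.8% (deterministic) or 71.6% (random residual), against 80.8% using observed data only.

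Simulations used 6,000 to 12,000 replicates for the level and 4,000 for power. With no missing data they gave 4.98% and 5.00%, so the set-up recovers the nominal level.

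**Sensitivity to the missing share.** The step from 480 to 400 implies 80/480 = 16.7% loss: 1.96 × 0.833 = 1.633, giving 10.2%.

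**Gradual dropout.** Let losses build up evenly over T1, T3 and T5 to 19.9%, with sequential deterministic imputation including arm (N = 480, correlation between visits 0.6 / 0.4):

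- T1: 6.3% / 7.2%. As a check, about 0.199/3 = 6.6% is missing at T1, and 1.96 × 0.934 = 1.83 gives 6.7%.
- T5: 10.4% / 11.2%.
- Average over the three visits: 7.6% / 8.2%.

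**With the remedy.** Multiple imputation (20 imputations, arm included, Rubin's rules) rejects 5.2% (N = 480) and 4.6% (N = 400). ANCOVA on observed cases rejects 5.1% and 4.8%. All are nominal within simulation error.

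**The case against.** The best defence is that the sentence does not say the gaps are filled once. It speaks of techniques in the plural, multiple imputation commonly runs on regression models, and a condensed article may leave the number of imputations and the pooling rule to the analysis plan. If multiple imputation with arm included is meant, the level is correct. That stands, and it makes the finding conditional. It does not remove it: the method named is, in ordinary usage, a single-imputation method, and both choices about arm then do harm.

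A reader might infer more than the article supports:

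- *That the test simply rejects 11% of the time.* This needs single imputation, arm in the imputation model, and all of the 19.9% missing at the tested visit. The article fixes none of these, and it does not give the follow-up length of the earlier study behind the 19.9%.
- *That the error always favours the device.* With arm omitted it runs the other way.
- *That every adherence measure is equally exposed.* Refill rates are requested from pharmacies, and a missed visit need not remove them.
- *That quality-of-life and walk-test comparisons are distorted likewise.* The article assigns the repeated measures ANCOVA to adherence and names no test for those outcomes.
- *That the hospitalisation analyses are affected.* Dropout is ordinarily handled by censoring in log-rank and Cox analyses, and this calculation does not apply there.
- *That the plan will generate values for patients who have died.* The all-randomised rule combined with imputation leaves that open, but the article does not state it.

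**Conclusion.** The point holds in conditional form. As written, the plan imputes by regression for all randomised patients and provides nothing to carry imputation uncertainty into the ANCOVA of adherence. Read as single imputation, there are two outcomes:

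- **Arm in the imputation model:** the nominal 5% test could reject up to about 10-12% of the time with 19.9% missing at the tested visit. With gradual dropout the rate is about 6-7% at T1 and 10-11% at T5.
- **Arm omitted:** the level stays near 5%, and the estimated effect shrinks by about 20%.

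The damage is greatest for visit- and questionnaire-based adherence and may be smaller for refill rates. The figures rest on the assumptions listed with the calculation, in particular dropout that is random and equal between arms.

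**What to change.** Replace the imputation sentence with one of two options:

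1. A likelihood-based mixed model for repeated measures fitted to the observed adherence data, with arm, visit, arm-by-visit interaction and baseline value.
2. Multiple imputation with arm in the imputation model, combined by Rubin's rules.

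With either option, state that adherence values after a patient's death are not imputed. The mixed model does not settle this by itself, because it implicitly extrapolates past death unless the plan says what is being compared.

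The cost is a few lines of text and slightly more analysis work. Where arm would have been in a deterministic single-imputation model, intervals become up to about 25% wider (1/0.801 = 1.248). That is the correct width, so no real precision is lost.
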